### Study timeline

The study protocol consists of two main phases over 3 weeks: the screening and the treatment phase (Figure 1). The screening period will last 1 week; participants will be included in this phase according to the inclusion/exclusion criteria. Participants will be treated three times a week for 2 weeks, with different interventions among the groups.

**Figure 1 fig1:**
[figure not shown]
Flow diagram. AE, atopic eczema; EA, electroacupuncture; SEA, sham electroacupuncture; SAC, sham acupuncture.

### Screening phase

Patients with AE will be enrolled in the screening phase through a dermatological outpatient service, and physical examinations and inclusion evaluations will be performed. The trial’s eligible participants will be requested to complete a written informed consent form (including the procedures, risks, and options for quitting the study). The study will be thoroughly explained to the participants by a researcher with the required training. Participant must sign an informed consent form after giving their approval. An algorithm will separate patients randomly into the EA, SEA, and SAC groups.

### Treatment phase

Patients with AE will receive interventions during the treatment phase. Patients will be checked for visual analog scale (VAS), Eczema Area and Severity Index (EASI), Dermatology Life Quality Index (DLQI), serum IgE, adverse events, and compliance during the two-week therapy period, administered three times a week. After 2 weeks, all interventions will end. We will record demographic characteristics, medical and medication histories, images of skin lesions, personal life histories, vital signs, physical examinations, and adverse effects (among other data) (Figure 2).

**Figure 2 fig2:**
[figure not shown]
Schedule of enrollment, interventions, and assessments.

### The park sham device (PSD)

The PSD and Park sham needle (PSN) are purchased from AcuPrime.^1^ We chose the PSD to maximize the blinding of participants because it has a double-tubed system that attaches to a plastic base and the participant’s skin (Figure 3). Double-sided tape is used to secure the device to the plastic base and the participant’s skin. Initially, in its expanded (highest) position, the inner tube is lowered to the outer tube as the needle is lowered. A real acupuncture needle or a PSN can be stored inside the PSD. The PSN is stainless steel with a length measuring 25–50 mm and looks like and is packaged similarly to an acupuncture needle. When downward pressure is applied to the handle of the PSN, the needle glides into the handle, providing the illusion that it is piercing the skin. PSD is critical to prevent the PSN from falling away from the participant’s skin and keep them from noticing whether a PSN or an actual acupuncture needle is used.

**Figure 3 fig3:**
[figure not shown]
The park sham device attached to the skin.

### Intervention

All three groups will have the PSD placed by the researchers. It will be applied to standard acupuncture points in the EA and SEA groups and sham acupuncture points in the SAC group.

Participants in the EA group will receive acupuncture with PSD at the bilateral *Hegu* (LI4, located between the first and second metacarpals, at the midpoint of the radial aspect of the second metacarpal), bilateral *Quchi* (LI11, located at the lateral end of the transverse elbow stripe, flexing the elbow, at the midpoint of the line connecting the *Chize* (LU5) and the external humeral epicondyle), bilateral *Xuehai* (SP10, located on the medial thigh, flexing the knee, 2 cun [≈10 mm] above the medial end of the base of the patella, at the bulge of the medial head of the quadriceps), and bilateral *San Yinjiao* (SP6, located 3 cun [≈ 10 mm] above the tip of the inner ankle, on the posterior edge of the medial side of the tibia) (Figure 4). After skin disinfection, the acupuncture needles are inserted approximately 10–20 mm into the skin at a 90° angle.

**Figure 4 fig4:**
[figure not shown]
Location of verum acupoints and sham acupoints.

Achieving qi (a combination of sensations, including soreness, numbness, distention, heaviness, and other sensations) is considered an important part of obtaining the efficacy of acupuncture. Four pairs of electrodes are used: two each on bilateral *Quchi* (LI4) and *Hegu* (LI11) and two each on bilateral *Xuehai* (SP10) and *San Yinjiao* (SP6); they are all ipsilateral to one another. The duration of the EA stimulation is 30 min, with the current intensity of 1–5 mA with a continuous wave of 20 Hz (with the skin around the acupoints shivering mildly without pain). For 2 weeks straight, the participants will have three therapy sessions each week for a total of six sessions.

Participants in the SEA group will receive SEA with PSD but without energizing the electropuncture device. Procedures, electrode placements, and other treatment settings will be the same as those in the EA group but with no electricity output.

Participants in the SAC group will receive sham acupuncture with PSD and PSN at sham acupoints (non-meridian and non-acupuncture points). The sham acupoints selected for this study, based on reports from other scholars, are as follows: (33) The sham *Hegu* (LI11) is located at the dorsum of the hand, between the first and second metacarpals, 1 cun [≈10 mm] next to the midpoint of the radial side of the second metacarpal. The sham *Quchi* (LI4) point is at the midpoint between the locations of verum *Quchi* and *Chize*; the sham *Xuehai* (SP10) point is 1 cun [≈10 mm] lateral to the verum *Xuehai*; the sham *San Yinjiao* (SP6) point is at 3 cun [≈10 mm] above the tip of the lateral ankle, between the stomach and bile meridians.

Procedures, electrode placements, and other treatment settings will be the same as those in the EA group, but with no skin penetration, electricity output, or needle manipulation to achieve qi.

#### Basic treatment

Throughout the course of the trial, all patients will receive standard base treatment (health guidelines).Increase moisturizing of the skin: As a basic treatment, using a moisturizer is mandatory (34). The moisturizer should be applied to skin areas free from erosion, exudation, and dry non-lesion areas. A soft, fragrance-free moisturizer will be used in this study. Urea cream (purchased from Yueyang Hospital of Integrated Traditional Chinese and Western Medicine, H04050489) is recommended for patients with sensitive, dry skin.Standard bath: Generally, patients should rinse quickly for 5 min once daily in warm water (35–39°C). To prevent the skin from becoming dehydrated after showering, a moisturizer should be applied within 2 min. We recommend avoiding cleaning the skin with alkaline detergents.Avoiding factors that cause or worsen disease: Some diets might cause or aggravate disease for certain people. Avoiding these foods is advised.Some patients may have food allergies. When food allergies are discovered, certain foods should be avoided to avoid causing or exacerbating the disease.Maintain a moderately healthy lifestyle: patients should abstain from excessive stress and staying up late. Spicy and irritating foods should be avoided, and appropriate exercise should be performed. Patients should attempt to maintain regular bowel movements.

### Drug combination

#### Combination treatments permitted

Patients with co-morbidities or newly developed co-morbidities will be allowed to take specific medications/other treatments during the study, but only if the details are included in the medical record for analysis. The drug name (or other therapeutic name), dosage, frequency, and time of use are recorded for convenient summary and analysis.

#### Combination treatment prohibited

Other herbal medicinal preparations for the purpose of treating the disease.Other topical preparations containing drugs, including steroid preparations, coal tar, herbal preparations, etc.Antihistamines.Systemic steroid hormone therapy.Non-steroidal immunosuppressive agents.Photochemotherapy.Desensitization therapy.

### Outcome measures

#### Primary outcome measure

The proposed study’s primary outcome is improved VAS scores after 2 weeks of treatment. VAS scores are designed to be measured at the screening phase, after 1 week of treatment, and after 2 weeks of treatment. Pruritus, the main clinical symptom of eczema, can be scored separately on the VAS (35).

#### Secondary outcome measure

Secondary outcome measures include the EASI (36) and DLQI (37). The timeline for the efficacy evaluation is shown in Figure 2.

#### Safety evaluation

Several measures will be taken for safety, including the observation of vital signs, drug combination, physical examination, adverse events, and severe adverse events outcomes. The timeline for the safety evaluation is presented in Figure 2. If an adverse event occurs, the researchers must quickly attend to it and record the date of occurrence, severity, duration, and treatment measures. In the case of a serious adverse event, the researchers must take immediate action to ensure the safety of the participants, report to the principal investigators and Western Medicine and the Ethics Committee within 24 h, and determine if the participant should be withdrawn based on the condition.

### Data management and monitoring

All study data, including informed consent forms, will be collected and maintained in a dedicated database for medical research records and must be submitted by researchers at the end of the treatment phase. The principal investigators at the participating hospitals will be responsible for collecting the medical research records from the researchers and for reviewing and storing these records.

The data report adopts an electronic Case Report Form (eCRF); each center will assign a specific person to data entry. To ensure the quality and consistency of the source data and database input, two researchers will independently verify the source data with the eCRF data. In the case of any discrepancy, a query list will be created, and the researchers must respond to the query list to resolve the discrepancy. All documentation related to quality control will be maintained to allow for future objective evaluation of safety and critical efficacy outcomes.

### Statistical analysis

Professional statisticians developed a statistical analysis plan upon consultation with the primary investigators. The data will be stored in the Data Management Center of Jiangsu Famous Medical Technology Co. Ltd. and processed by in-house statisticians blinded to group allocation.

All statistical analyses are performed using R [version 4.1.3; R Core Team (2022). R: A language and environment for statistical computing. R Foundation for Statistical Computing, Vienna, Austria^2^]. Statistical significance is set at value of *p* < 0.05. The intention-to-treat analysis population, consisting of all participants who pass the randomization stage, will be the primary population for demographic and other baseline characteristics, compliance, efficacy analysis, and safety analysis.

The analytical methods will be combined with descriptive and comparative analyses. Qualitative data will be described by frequency tables, percentages, or composition ratios; comparative analyses will be conducted using the chi-squared test, Fisher’s exact test, Wilcoxon rank-sum test, Cochran–Mantel–Haenszel test, and weighted least-squares covariance. Quantitative data will be described as the mean, standard deviation, median, quartile, minimum, and maximum. The *t*-test will be used for comparative analysis of data with normal distributions and with Satterthwaite correction if the variance is uneven. Quantitative data exhibiting a non-normal distribution on the Wilcoxon rank-sum test will be analyzed using the Wilcoxon signed-rank sum test and covariance generalized linear models. A sensitivity analysis for the primary outcome with the most conservative data (the worst or best outcome of that indicator in the group) will assess the robustness of the missing data at random assumption. A multiple imputation will be used to impute missing values.

The hypothesis test is two-sided; the test statistics and their corresponding *p*-values will be reported.

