### Sample size

According to a previous study (32), the mean itch intensity was taken as 35.7% for the EA group, 40.4% for the sham electroacupuncture (SEA) group, and 45.9% for the sham acupuncture (SAC) group, with *α* = 0.05, test efficacy 1-β = 0.8, two-sided test, using the estimation of sample size formula for comparing more than two treatment groups [referring to 
$n=2{\left(\sigma \frac{Z_{1-\alpha /\left(2\tau \right)}+Z_{1-\beta }}{\mu_{A}-\mu_{B}}\right)}^{2}$
, 
$1-\beta =\Phi \left(Z-Z_{1-\alpha /\left(2\tau \right)}\right)+\Phi \left(-Z-Z_{1-\alpha /\left(2\tau \right)}\right)$
, 
$Z=\frac{\mu_{A}-\mu_{B}}{\sigma \sqrt{\frac{2}{n}}}$
, where Φ is the standard normal cumulative distribution function, 
$\mu_{A}\;\mathrm{and}\;\mu_{B}$
 representing the mean of any two groups, and n is the sample size of a pair of τ comparisons (taking the maximum value)]. Consequently, the sample content was calculated to be 35 cases per group and 105 cases for the three groups. Assuming a 20% dropout rate of patients at follow-up, we calculated the sample size to be 44 cases for each group and 132 participants for the three groups (EA, SEA, and SAC). Participants will be recruited from two research centers, each targeting 66 participants.

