We propose a prospective, multicenter, randomized controlled study of AE. The multicenter model considers the effect of environmental factors and individual participant characteristics on trial results, providing more reliable clinical evidence. We designed three arms to compare the effectiveness of EA and acupuncture and to establish the genuineness and credibility of the acupoints while eliminating any potential placebo effect. The objective VAS score was adopted as the primary outcome measure, and the EASI and DLQI scores as the secondary outcome measures, which should improve the reliability of the results. In addition, physical examination, personal life history, safety evaluation, patient satisfaction, and other outcome measures have been added. Keeping participants closer to the clinic helps track the disease progression in a clinical setting.

The study design has limitations. First, the sample size is only 132 participants. Second, the study duration is limited to 3 weeks without a follow-up period. Observing the long-term effects of the EA anti-itch technique on the progression of AE with a limited sample size and follow-up period will be challenging. However, we will use unique experimental designs and outcome measures to improve the accuracy and sensitivity of this study to mitigate these limitations.

In summary, this multicenter, randomized, sham electroacupuncture–controlled study will assess the effect on pruritus, clinical efficacy, and safety of the acupuncture antipruritic technique in AE. We will also establish a multicenter clinical registration platform and evaluate clinical evidence by assessing the treatment’s therapeutic benefits (clinical effectiveness with no adverse side effects). The findings will aid decision-making for managing and treating AE and offer crucial data that could be integrated into future clinical recommendations.

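### The sample size uses a multiplicity-adjusted critical value, but the analysis section sets a single p < 0.05 threshold with two-group tests and states no adjustment, gate or primary contrast

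*Protocol article*

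**What the plan says.** The Sample size section gives α as "0.05, test efficacy 1-β = 0.8, two-sided test", "using the estimation of sample size formula for comparing more than two treatment groups". The critical value in that formula is Z at 1−α/(2τ). The two means are described as "representing the mean of any two groups, and n is the sample size of a pair of τ comparisons (taking the maximum value". The assumed itch means are "35.7% for the EA group, 40.4% for the sham electroacupuncture (SEA) group, and 45.9% for the sham acupuncture (SAC) group". The result is reported as "the sample content was calculated to be 35 cases per group and 105 cases for the three groups", raised to 44 per group and 132 in total for 20% dropout. Neither τ nor σ is given a value.

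The Statistical analysis section says "Statistical significance is set at value of" p < 0.05, with two-sided tests. For normally distributed quantitative data it names the t-test, with a Satterthwaite correction for unequal variances. For non-normal data it names Wilcoxon tests and generalized linear models.

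The Primary outcome section makes VAS improvement after 2 weeks primary but does not say which pair of arms decides the trial. The Discussion gives the arms more than one purpose: "We designed three arms to compare the effectiveness of EA and acupuncture and to establish the genuineness and credibility of the acupoints".

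**The concern.** The two sections appear to follow different error-rate rules. Dividing α by τ in the sizing formula treats 0.05 as the error rate for the whole set of pairwise comparisons. A single p < 0.05 threshold attached to two-group tests reads most naturally as 0.05 for each comparison. With three arms, more than one contrast of interest and no deciding contrast, a positive result on any pair could be reported as the trial's success. The type I error of the primary conclusion is then above the design's 5%, and the analysis is not the one for which the sample size was justified.

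**Working it through.** **Inputs.** From the Sample size section: α = 0.05 two-sided, power 0.80, means 35.7, 40.4 and 45.9, 35 per group, 20% dropout. From the Statistical analysis section: p < 0.05, two-sided, two-group tests. Assumption: τ = 3, because three arms have three pairs and the formula refers to any two groups. The article gives no number.

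**1. The plan's own figures.** Dropout: 35/(1 − 0.20) = 43.75, rounded up to 44; 3 × 44 = 132. This reproduces. The 35 cannot be checked, because n = 2[σ(z₁₋α/(2τ) + z₁₋β)/Δ]² needs σ. The pairwise differences are 40.4 − 35.7 = 4.7, 45.9 − 40.4 = 5.5 and 45.9 − 35.7 = 10.2. Solving backwards for σ at n = 35:

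| τ | Δ = 4.7 | Δ = 5.5 | Δ = 10.2 |
|---|---|---|---|
| 1 | 7.02 | 8.21 | 15.23 |
| 3 | 6.08 | 7.11 | 13.19 |

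For Δ = 4.7, σ = 6 with τ = 3 and σ = 7 with τ = 1 both give exactly 35. The figure of 35 therefore does not show which τ was used.

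**2. Family-wise error of unadjusted tests, all three means equal.**
- Any of three pairs at 0.05: P(studentized range for 3 groups > 1.96 × √2) = 12.23%. Simulated t-tests (400,000 trials) give 12.20% at n = 35 and 12.26% at n = 44. The contrasts share arms and are correlated, so this is below the independence figure, 1 − 0.95³ = 14.3%.
- Only EA vs SEA and EA vs SAC: 9.0% at n = 35, 9.1% at n = 44.
- Each of three pairs at 0.05/3 = 0.0167: 4.4%.
- Pairwise tests at 0.05 only after a significant overall F-test: 5.0% at n = 35, 5.1% at n = 44.

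**3. Power for the contrast that fixed n, at 35 per group.** The expected z-statistic is z₁₋α/(2τ) + z₀.₈₀, and power is Φ(expected z − critical value).
- Sized with τ = 3, tested at 0.0167: 80% by construction.
- Sized with τ = 3, tested at 0.05: 2.394 + 0.842 = 3.236; Φ(3.236 − 1.960) ≈ 90%.
- Sized with τ = 1, tested at 0.0167: 1.960 + 0.842 = 2.802; Φ(2.802 − 2.394) = Φ(0.408) ≈ 66%. At 44 per group with no dropout: 2.802 × √(44/35) = 3.141; Φ(3.141 − 2.394) ≈ 77%.

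**The case against.** The strongest reply is that the article refers to a separate statistical analysis plan, where a multiplicity procedure and order of contrasts would normally be found. It never says that pairwise tests are unadjusted. A general p < 0.05 threshold is compatible with adjusted p-values or with 0.05 as a family-wise level, and the Sample size section itself starts from α = 0.05 before dividing it. Some of the listed methods, such as generalized linear models and weighted least squares, can handle three groups.

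Much of this stands. The absence of multiplicity detail alone would be no finding in a condensed article, and an adjustment in the unseen plan is possible. What remains is that the article does not leave the matter open. It fixes a divided α for sizing and an undivided threshold for analysis, and nothing in the text connects them. The three-group methods are not described as a gate.

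A reader might also infer three stronger things that the article does not support:
- That the trial's false-claim rate simply is 12%. This needs any of three contrasts to count as success, which no section says. SEA vs SAC contains no EA arm, so a false positive there is not a false EA claim.
- That n was sized at 0.0167. τ = 3 is inferred and σ is missing.
- That tightening the threshold costs no power. This fails if τ = 1 was used.

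**Conclusion.** The point holds as a conflict between two stated rules. Followed as written, the analysis gives a family-wise error under the global null of about 12% when any of the three contrasts can count, and about 9% when only the two EA contrasts count. It is at or below 5% only under a rule the article does not state, such as EA having to beat both shams or a single primary contrast. The error figures assume unadjusted pairwise tests at two-sided 0.05 and equal arms of 35 to 44. They do not depend on σ. The level at which n was actually computed cannot be established from the article.

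**What to change.** In the Statistical analysis section, name EA vs SEA and EA vs SAC on week-2 VAS as the contrasts that carry the EA claim. State that 0.05 is family-wise, controlled over the same τ comparisons as in the Sample size section. Holm's procedure is one suitable choice. Its first step is 0.05/3 = 0.0167 if all three pairs form the family, or 0.05/2 = 0.025 if only the two EA contrasts do, with SEA vs SAC then supportive. In the Sample size section, state τ and σ so that the 35 can be checked.

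The cost is a paragraph of wording and a stricter per-contrast threshold. No power is lost against the stated 80% if n was computed with τ at least as large as the tested family. If a smaller τ was used, the stated power must be restated; in the τ = 1 case with a first step of 0.0167 it is about 66% for the sizing contrast at 35 per group. The change should be made before any unblinded analysis.

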### Randomization and allocation

Once eligibility is confirmed and consent is obtained, participants will be block-randomized using a non-stratified, permuted block of varying lengths (*n* = 2 blocks; patient distribution = 1:1:1) for each group. Independent statisticians will provide computer-generated random sequences. Distribution will be conducted using a central web-based interactive randomization service system; the patients will be assigned randomly to three groups. Participant identification numbers will be provided to make identification easier throughout the trial. The researchers who perform random grouping will need to log onto the website to view the grouping situation of each eligible participant. The authors have no access to information that could identify individual participants during or after data collection.

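### Safety is analysed primarily in all randomised participants, so anyone who never has a study session slightly lowers the adverse event rates; a treated set grouped by procedure received would suit safety better

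*Protocol article*

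**What the plan says.** The Statistical analysis section names a single population, the intention-to-treat set, "consisting of all participants who pass the randomization stage". It then states that this set "will be the primary population for demographic and other baseline characteristics, compliance, efficacy analysis, and safety analysis". The Safety evaluation section lists what will be observed and recorded but gives no other population. No set restricted to treated participants, and no grouping by procedure received, is named in the article.

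The number randomised is given under Sample size: "we calculated the sample size to be 44 cases for each group and 132 participants for the three groups". Allocation is equal ("patient distribution = 1:1:1", Randomization and allocation). For the EA arm the Intervention section states that "the participants will have three therapy sessions each week for a total of six sessions". The Study timeline section allots one week to screening before treatment, and the Screening phase section describes random assignment within that phase.

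**The concern.** Analysing everyone as randomised generally pulls a comparison towards no difference. For efficacy that is cautious; for harm it works the other way. A person who never attends a session adds one to the denominator and nothing to the count of treatment-related events. A person who receives another arm's procedure has any event credited to the assigned arm.

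Non-starters are plausible here. Because assignment is described within a screening week, there can be a gap between randomisation and the first session. Wrong delivery is also possible, since the arms differ in needle type, point location and whether the device is switched on, and masked participants may not notice an error.

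Safety is a stated aim in the abstract, the introduction and the closing summary of the discussion, so the absolute event rates will be read as a result in their own right. The rule is written into the article, so this is not a detail left to an unseen analysis plan.

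**Working it through.** **Reproducing the plan's own figure.** The base size is given as follows: "the sample content was calculated to be 35 cases per group and 105 cases for the three groups". The allowance is introduced by "Assuming a 20% dropout rate of patients at follow-up". Then 35 / (1 − 0.20) = 43.75, rounded up to 44, and 3 × 44 = 132. This agrees with the article, so 44 per arm is the denominator that the stated rule would use.

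**Inputs for the check**
- Randomised per arm: 44 (Sample size).
- Non-starters per arm, k: not given. Assumed 0 to 4.
- Participants with a treatment-related event, x: not given. Six is used as an illustration; the relative result does not depend on it.
- Non-starters contribute no treatment-related events.

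**Within one arm.** The rate under the stated rule is x / 44. The rate among those treated is x / (44 − k). The first divided by the second is (44 − k) / 44, so the relative understatement is k / 44.

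| k | Treated | Rate on 44 | Rate on treated | Relative understatement |
|---|---|---|---|---|
| 0 | 44 | 6/44 = 13.6% | 13.6% | 0% |
| 1 | 43 | 13.6% | 6/43 = 14.0% | 2.3% |
| 2 | 42 | 13.6% | 6/42 = 14.3% | 4.5% |
| 4 | 40 | 13.6% | 6/40 = 15.0% | 9.1% |

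In absolute terms the gap is 14.29 − 13.64 = 0.65 percentage points at k = 2, and 15.00 − 13.64 = 1.36 points at k = 4.

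**If no events are seen.** The one-sided 95% upper limit is 1 − 0.05^(1/n): 6.6% for n = 44, 6.9% for n = 42 and 7.2% for n = 40. Counting non-starters makes the bound look slightly tighter than the exposed participants support.

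**Between arms.** Write f = (44 − k) / 44 for each arm.
- With equal f, the rate ratio is unchanged because f cancels, and the risk difference is multiplied by f. At k = 4 in both arms it shrinks by 9.1%.
- With unequal f, the ratio is multiplied by f(EA) / f(sham). Four non-starters in EA and none in sham gives 40/44 = 0.91; the reverse gives 44/40 = 1.10.

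**Wrong procedure delivered.** Someone assigned to EA but given a sham procedure tends to lower the EA rate. Someone assigned to sham but given EA can raise the sham rate. Both draw the arms together. This is a different mechanism from the diluted denominator and does not lower every rate.

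**The case against.** Four points can fairly be made against this.

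1. *Calling a set primary does not make it the only one.* The article refers to a statistical analysis plan, which may hold a secondary treated set and rules for wrong treatment. A reader might infer that safety will never be analysed in treated participants; the article does not say so. What stands is narrower: the set that it names first for safety is the less suitable one.

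2. *The planned dropout is not a rate of non-starting.* A reader might apply the 20% and suppose that nine of 44 per arm go untreated. The Sample size section describes dropout at follow-up, and most of the drop-out criteria under Eligibility criteria concern events during treatment or during the trial. Those people would usually have had a session and would remain in a treated set. The documents do not support nine, so it is not used here.

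3. *The diluting group is people with no session, not people without needle or current.* A reader might take the sham participants as diluting the rates. By design, the sham acupuncture arm (SAC) has neither skin penetration nor current, and the sham electroacupuncture arm (SEA) has no current. Both were treated as planned and belong in any safety set.

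4. *The comparison between arms may hardly move.* Participants are masked, so non-starting should be roughly balanced, and balanced dilution leaves the ratio alone. A reader might infer that the rule makes EA look safer relative to sham. Through the denominator that follows for the ratio only if non-starting is unbalanced, and nothing in the article suggests that it would be.

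Randomisation also follows confirmed eligibility and consent, and treatment lasts only two weeks, so few or no non-starters is a realistic outcome.

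**Conclusion.** The point holds as a minor one. The article fixes the all-randomised set as the primary population for safety. The consequence is a small understatement of absolute adverse event rates and risk differences, together with some blurring of the EA versus sham contrast if anyone receives the wrong procedure. With an assumed 0 to 4 non-starters of 44 per arm, the understatement is 0% to 9% in relative terms, and zero if everyone starts.

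This rests on the assumed range of non-starters and on their having no treatment-related events. If events of any cause are also recorded in non-starters and counted, the dilution is smaller for that tabulation. The documents support neither a large bias nor a distorted rate ratio between arms.

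**What to change.** In the Statistical analysis section, keep the intention-to-treat set as primary for baseline characteristics and efficacy. For safety, state that the primary population is all participants who received at least one study session (EA, SEA or SAC), grouped by the procedure actually received.

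The cost is one sentence and one population flag in the dataset. The small downside is that grouping by procedure received departs from the randomised comparison for anyone wrongly treated. List each such case with the assigned arm, the procedure received and any events, so that a reader can see whether it matters. Reporting the number randomised but never treated in each arm would let the reader put the true value of k into the calculation above.

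As a separate matter, the Blinding section removes from analysis the data of participants whose allocation concealment is broken before the end of the trial. The new sentence should be worded together with that rule so that the two do not conflict over who is in the safety set.
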